**Figure 2 F2:**
[figure not shown]
Home display page in smartphone application.

**Figure 3 F3:**
[figure not shown]
Chart display of daily step counts in smartphone application.

Once baseline week data collection is completed, those assigned to the control group are encouraged to try to walk an additional 30 minutes per day along with their normal activity (the equivalent of 10,000 steps) [14] as an exercise goal. They are also issued with the Irish Heart Foundation ‘Be Active’ physical activity promotion brochure [13] by post or Email. Control group participants will then be contacted after two weeks and at the end of the of the follow-up period by SMS and mobile phone and are asked to forward, using a ‘share data’ function within the smartphone application, all daily step count data up to that point. Finally they are instructed to keep their phone charged and to always carry it during walking hours.

### Choice and description of the smartphone application

The team of researchers trialed various smartphone applications in an attempt to source a suitable autonomous, literacy-friendly and simple to use application, which possessed the key attributes that had already been identified in previous work [15], as important in applications which are designed to promote physical activity [16]. With evidence in literature on the benefits of using pedometers for promoting physical activity and walking interventions [4], researchers combined a list of potentially suitable iPhone and Android pedometer applications. As the Android operating system allowed the application to run continuously with or without interaction by the user it was decided to focus on the Android platform only. After pilot testing, the smartphone application Accupedo by Corusan [17] was chosen for study as it provided the most comprehensive list of advantages in applications of this type. These advantages include: easy to download; user-friendly; live feedback of step count to user; visually appealing graphic display of step count history with goal setting and goal achievement feedback; data sharing ability; inexpensive (once off purchase fee of €3.29 per user) and finally the application can run autonomously in the background, allowing researchers to monitor activity without user interaction or effort. At the time the trial began this smartphone application was only available on Android smartphone platforms. Accupdeo is now available on Android and iPhone platforms.

### Outcomes

The primary outcome variable is step count, measured daily for a week prior to treatment assignment (that is, baseline) and subsequently for a seven week follow-up period. Seven secondary outcomes will be measured at baseline and at the end of the follow-up period, namely: systolic blood pressure; diastolic blood pressure; resting heart rate; BMI; mental health as measured by HADS score; quality of life as measured by ED-5D and EQ-VAS. Table 1 outlines the definitions and measurement techniques for each of these secondary outcomes.

### Analysis plan

Daily step count (primary outcome variable) will be collected longitudinally as described above. All participants will also be invited back for follow-up testing (secondary outcome variables) within one week of finishing the trial. At this follow-up visit, to evaluate the effects of the trial on the secondary outcome measures, data on the same clinical, anthropometric and psychological variables measured at baseline (systolic blood pressure, diastolic blood pressure, resting heart rate, BMI, mental health as measured by HADS score, quality of life as measured by ED-5D and EQ-VAS) will be collected.

Baseline data will be compared across the two arms using suitable numerical summaries and graphical techniques. Functional data analysis techniques, using P-spline smoothers, will be used to graphically represent the eight week daily changes in step count in order to identify a suitable weekly summary statistic.

The effectiveness of the intervention will be assessed using a linear mixed model to compare the change in the primary outcome (within subjects and between treatments) when measured as the mean, median and total weekly steps while adjusting for the following covariates as appropriate: baseline step count, age, gender, socioeconomic status as measured by “medical card eligibility”, BMI, mean systolic blood pressure, mean diastolic blood pressure, mean resting heart rate, mental health as measured by HADS score, quality of life as measured by ED-5D and EQ-VAS and smartphone literacy as measured by whether the participant had activated Email on their smartphone. Those below a certain income level (for example, $238/€184 per week net income for a single person aged up to 65 years who is living alone or $261/€202 per week net income for a single person aged 66 years and over who is living alone) [18] are said to be ‘medical card eligible’ which allows access to family doctor or general practitioner (GP) services, community health services, dental services, prescription medicine costs, hospital care and a range of other benefits free of charge. Therefore, medical card eligibility provides socioeconomic data measured atan individual level. The selection of explanatory variables for inclusion in the final model will be based on a combination of clustering, tree-based methods and variable selection techniques.

It will be assumed that missing data are missing at random and therefore accounted for in the mixed model. The validity of this assumption will be investigated by looking at the missing data patterns and by modeling the probability of missing data based on the explanatory variables available. The sensitivity of the final conclusions to this assumption will be assessed using multiple imputations via chained equations and predictive mean matching assuming data are missing not at random. Model checking will be performed using suitable model diagnostics and residual plots. All statistical analyses will be performed using the software packages SPSS version 21.0, R version 2.14.3 and Minitab version 16.2.

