**Methods/design:**

A two-group, parallel randomized controlled trial (RCT) with a main outcome measure of mean difference in daily step count between baseline and follow up over eight weeks. A minimum of 80 active android smartphone users over 16 years of age who are able to undertake moderate physical activity are randomly assigned to the intervention group (n = 40) or to a control group (n = 40) for an eight week period. After randomization, all participants will complete a baseline period of one week during which a baseline mean daily step count will be established. The intervention group will be instructed in the usability features of the smartphone application, will be encouraged to try to achieve 10,000 steps per day as an exercise goal and will be given an exercise promotion leaflet. The control group will be encouraged to try to walk an additional 30 minutes per day along with their normal activity (the equivalent of 10,000 steps) as an exercise goal and will be given an exercise promotion leaflet. The primary outcome is mean difference in daily step count between baseline and follow-up. Secondary outcomes are systolic and diastolic blood pressure, resting heart rate, mental health score using HADS and quality of life score using Euroqol. Randomization and allocation to the intervention and groups will be carried out by an independent researcher, ensuring the allocation sequence is concealed from the study researchers until the interventions are assigned. The primary analysis is based on mean daily step count, comparing the mean difference in daily step count between the baseline and the trial periods in the intervention and control groups at follow up.

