### Hypothesis

The formal null hypothesis to be tested in this study is that there is no change in mean daily step count between baseline and follow-up amongst participants in the intervention and control groups. The alternative hypothesis is that the intervention group using the smartphone application will show a significant increase in mean daily step count between baseline and follow-up in comparison to the control group.

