### Sample size and power calculation

The sample size required for the proposed RCT is 80 participants. The sample size is based on the following assumptions. Assuming that the mean daily step count at baseline is 4,700 steps, it is estimated that over the length of the trial, the mean step count in the control arm will reduce by 470 (a 10% reduction) and increase by 940 (a 20% improvement) amongst those receiving the intervention [11]. Using a two-sample comparison of the mean improvement between the arms, a sample size of 33 subjects per arm is required to have 80% power at the 0.05 significance level to detect a difference in the mean improvement of 1,410 between the arms, with an estimated standard deviation of the improvement in step count of 2,000. To account for dropouts or loss of patients to follow-up, the sample size will be adjusted upward from 33 to 40 per group. All analyses will be conducted according to the intention-to-treat principle.

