### Description of interventions/comparison groups

The study is a two-group, parallel randomized controlled trial. As such, following the screening visit, eligible participants are randomly assigned to the intervention and control groups in an equal ratio of 1:1. All participants have the smartphone application downloaded free of charge onto their smartphone but not made visible to the user. For the following week after the screening visit (baseline week), all participants are asked to carry their smartphone during walking hours and continue to operate at their normal physical activity levels. All participants are then contacted by SMS and mobile phone at the end of baseline week and asked to Email their baseline step count data to the research team using a ‘share data’ function within the smartphone application.

Once baseline week data collection is completed, those assigned to the intervention group are instructed on how to turn on the smartphone application display (Figure 2) and how to position the display widget on the smartphone home screen. Intervention group participants receive a short instruction by phone on the usability features of the smartphone application settings, feedback graphs (Figure 3), and continuous feedback on their daily step count. Intervention group participants are encouraged to interact with the smartphone application and are encouraged to try to achieve the physical activity goal of 10,000 steps per day. They are also issued with the Irish Heart Foundation ‘Be Active’ physical activity promotion brochure [13] by Email. Intervention group participants are then contacted after two weeks and at the end of the of the follow-up period by SMS and mobile phone, and asked to forward, using a ‘share data’ function within the smartphone application, all daily step count data up to that point. Finally they are instructed to keep their phone charged and to always carry it during walking hours.

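### The analysis plan reopens the named primary measure (mean daily step count) to a choice made from the outcome data and among three summaries, so the 0.05 level is not guaranteed

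*Protocol article*

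**What the plan says.** Three places in the protocol article point to one measure.

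- Abstract, Methods/design: "The primary analysis is based on mean daily step count", compared between the baseline and trial periods.
- Hypothesis: the alternative is that the intervention group "will show a significant increase in mean daily step count between baseline and follow-up in comparison to the control group".
- Sample size and power calculation: "a sample size of 33 subjects per arm is required to have 80% power at the 0.05 significance level". The target is a between-arm gap of 1,410 steps in mean improvement, and the assumed SD of that improvement is 2,000 steps.

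The Outcomes section is looser. It gives the primary variable as step count, recorded daily for a baseline week and then for seven weeks of follow-up, and names no summary.

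The Analysis plan section departs from the single measure in two steps. First, smoothed curves "will be used to graphically represent the eight week daily changes in step count in order to identify a suitable weekly summary statistic". Second, a linear mixed model compares how the primary outcome changes "when measured as the mean, median and total weekly steps". The section does not say which summary decides, makes no multiplicity adjustment, and does not say whether the plots are pooled or split by arm.

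**The concern.** The eight weeks being plotted include the seven follow-up weeks, which are the outcome data. A summary picked after seeing them can be picked, knowingly or not, because it separates the arms better. Listing three summaries with none ranked first has the same effect if whichever reaches p < 0.05 may be reported as the primary result. In either case the single 0.05 level on which the sample size rests no longer describes the test performed.

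The choice can matter in practice. Mean and total agree only when every day is recorded, and recording depends on the phone being charged and carried. A weekly total therefore reflects carrying as well as walking.

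This is not detail that an article leaves to a separate analysis plan. The article states a rule, and the rule conflicts with the measure it names elsewhere.

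**Working it through.** **1. Reproduce the plan's own figure.** Inputs from the Sample size section: difference 1,410 steps, SD 2,000, alpha 0.05, power 80%. Allocation is 1:1 (Description of interventions). Sidedness is not stated.

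- Normal formula, two-sided: n = 2 × [2,000 × (1.960 + 0.842) / 1,410]² = 31.6, so 32 per arm.
- Two-sample t-test version: 32.57, so 33 per arm, which is the stated figure. Power at 33 is 0.805.
- One-sided 0.05 would need only about 25 per arm, so the stated figure implies a two-sided test.
- Dropout: 33 / (1 − 0.175) = 40, as stated.

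The sample size is correct for one test, on mean improvement, at two-sided 0.05.

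**2. Bound the inflation.** If any of three independent tests could count, the error would be 1 − 0.95³ = 14.3%. These tests are far from independent. With all seven days recorded, weekly total = 7 × weekly mean, so those two give the same t statistic and only the median adds anything. For three equally correlated tests the any-of-three rate is 9.8% at correlation 0.8 and 8.3% at 0.9.

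**3. Simulate under the null.** Assumptions, none of them from the article: 33 per arm; log-normal daily steps centred on 4,700; log-scale SDs of 0.45 (person), 0.25 (week) and 0.55 (day); missing-day rate varying by person. One baseline week and seven follow-up weeks were generated. The test was a t-test on the seven-week average minus baseline, with 5,000 runs per setting.

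| Days missing (average) | Mean alone | Median alone | Total alone | Any of three | Correlation, mean with total |
|---|---|---|---|---|---|
| 0% | 4.8% | 4.3% | 4.8% | 6.6% | 1.00 |
| 10% | 4.8% | 5.0% | 5.3% | 8.4% | 0.94 |
| 25% | 5.0% | 5.0% | 5.3% | 9.0% | 0.86 |
| 40% | 4.7% | 4.6% | 4.5% | 9.1% | 0.78 |

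Monte Carlo standard error for the any-of-three column is about 0.4 points: √(0.09 × 0.91 / 5,000) = 0.004.

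Repeating the null simulation under assumed variances gave 6.6 to 7.3% with complete days and 8.4 to 9.0% with 0 to 30% missing.

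**4. Vary the decision rule.** A separate null simulation used gamma daily steps, baseline-adjusted ANCOVA, 33 per arm and 4,000 runs.

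| Rule | Complete days | 0–30% missing |
|---|---|---|
| Mean alone | 5.1% | 4.8% |
| Summary chosen from pooled, arm-blind data (least skewed) | 5.5% | 5.0% |
| All three must agree | 3.3% | 1.7% |
| Any of three may count | 7.4% | 8.4% |

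**5. Cost of the alternative remedy.** If all three stayed eligible under a Bonferroni split (0.05 / 3), the normal formula gives 43 per arm before dropout. Power at 33 per arm would be about 68%.

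**The case against.** The strongest reply is that the article does name a primary measure. The mean is the only version tied to the hypothesis, the alpha and the sample size. The three summaries could be meant simply as consistency checks. The summary is to be found from a graph rather than from p-values, and a choice made on pooled, arm-blind data leaves the error close to 5%. Requiring all three to agree would push it below 5%. With complete weeks, three summaries are really two.

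Most of this stands, and it limits the point. It does not remove it, because the Analysis plan section neither repeats the mean as the deciding measure nor says the plots are arm-blind.

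A reader might infer three stronger things that the article does not support.

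- *That no primary measure is specified.* The Abstract, Hypothesis and Sample size sections specify one; the fault is that the Analysis plan reopens it.
- *That the 5% level is certainly lost.* No rule in the article lets the smallest p-value decide. The loss is conditional on how the choice is made.
- *That the time contrast is also open, between the follow-up average and the last week.* The Abstract compares the baseline and trial periods, and Outcomes gives step count a seven-week follow-up. Measurement at the end of follow-up is specified there only for the secondary outcomes. No section proposes a last-week step comparison, so no inflation should be attributed to one.

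**Conclusion.** The point holds as an internal contradiction with a conditional consequence. The article powers and frames the trial on mean daily step count, then allows outcome data to inform the summary and assesses three summaries without saying which decides.

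If the choice is made knowing the arm differences, or if any of the three may count, the 0.05 level is not guaranteed. For the any-of-three rule, type I error is about 6.6 to 7.3% with complete days and about 8 to 9% with 0 to 30% of days missing, against about 5% for the mean alone. If the mean governs, or the choice is made blind to arm, the error stays near 5%.

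The sizes rest on assumed step-count distributions, variances and missing-day rates, and on a t-test or ANCOVA in place of the planned mixed model. The direction does not depend on those details; the exact figures do. The sample size calculation itself is not in error.

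**What to change.** In the Analysis plan section:

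1. Name one primary analysis: the between-arm difference in change in mean daily step count, from the baseline week to the seven-week follow-up period, tested at two-sided 0.05. The linear mixed model can stay as the method.
2. Make weekly median and weekly total named sensitivity analyses that cannot replace the primary result.
3. Keep the P-spline plots as description only, and delete the closing clause that gives their purpose as finding a weekly summary statistic.

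This should be settled before anyone examines the follow-up step data. The cost is one paragraph of wording, with no extra data or participants, and 33 per arm (40 with dropout) stands. The only thing given up is the freedom to choose the summary later.

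### The covariates of the effectiveness model are to be chosen on the trial data by an unspecified mix of methods, with none fixed in advance, which leaves the model open and permits understated standard errors

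*Protocol article*

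**What the plan says.** The Analysis plan section makes a linear mixed model the assessment of effectiveness. The model compares the change in step count between arms "while adjusting for the following covariates as appropriate: baseline step count, age, gender, socioeconomic status", and the list then continues. Counting EQ-5D and EQ-VAS separately, there are 12 candidates: baseline step count, age, gender, medical card eligibility, BMI, systolic pressure, diastolic pressure, resting heart rate, HADS, EQ-5D, EQ-VAS and smartphone literacy.

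The same section then gives the rule for choosing among them. The variables for the "final model will be based on a combination of clustering, tree-based methods and variable selection techniques". It does not say which algorithms are used, in what order, at what threshold, or how disagreement between them is settled. It does not say whether treatment is in the model during selection.

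The sample size section rests on a simpler test: "Using a two-sample comparison of the mean improvement between the arms, a sample size of 33 subjects per arm is required". That test has no covariates.

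**The concern.** In a 1:1 randomised comparison, adjustment is not needed to remove confounding; its purpose is precision. That benefit comes from choosing prognostic covariates in advance. If they are chosen on the same data that then estimate the treatment effect, the reported p-value and interval treat the chosen set as though it had always been fixed.

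Two things are at stake:

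- **The model is undetermined.** Two competent analysts could follow the protocol and reach different final models and different treatment estimates. Nobody could show afterwards that the reported one was the planned one.
- **The standard error may be too small.** If treatment sits in the model while covariates are added or removed, the procedure tends to favour covariates whose chance imbalance between arms moves the treatment estimate. The estimate then varies more than its standard error says.

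**Working it through.** **1. The plan's own figure.** Inputs from the sample size section: "80% power at the 0.05 significance level", "to detect a difference in the mean improvement of 1,410 between the arms" and "with an estimated standard deviation of the improvement in step count of 2,000". Allocation is 1:1.

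- Normal approximation, two-sided: n = 2 × [2,000 × (1.960 + 0.842) / 1,410]² = 31.6, so 32 per arm.
- Two-sample t-test: 32.57, so 33 per arm, with power 80.5% at 33. This matches the protocol.
- Dropout: 33 / 40 = 0.825, an allowance of 17.5%.

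The sample size is sound for an unadjusted comparison and does not depend on covariate selection. The analysable total therefore lies between 66 (33 per arm) and 80 (40 per arm).

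**2. Null simulation.** There were 4,000 simulated trials per setting with no treatment effect, N = 66 or 80, and 12 candidate covariates. Three inputs are assumptions, not protocol figures: pairwise covariate correlation 0.2, baseline explaining 0% or 30% of outcome variance, and ordinary regression on a change score in place of the mixed model. The Monte Carlo standard error near 5% is √(0.05 × 0.95 / 4,000) = 0.34 percentage points. The SE ratio is the model standard error divided by the true standard deviation of the treatment estimate.

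| Covariate rule | Type I error over the four settings | SE ratio |
|---|---|---|
| Fixed: baseline only, or all 12 | 4.6–5.3% | 0.98–1.01 |
| Forward AIC, treatment left out of the selection step | 4.7–5.1% | 0.99–1.00 |
| Forward p < 0.05, treatment in the model | 5.3–6.1% | 0.95–0.98 |
| Forward AIC, treatment in the model | 6.4–7.4% | 0.91–0.95 |
| Smallest p-value among six models | 7.5–10.0% | 0.79–0.86 |

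The setting N = 66 with 0% explained shows the mechanism. The reported standard error is almost the same whether treatment is in or out of the selection step (0.2395 and 0.2396). The true spread is not: 0.2638 with treatment in, 0.2424 with it out. The ratios are 0.2395 / 0.2638 = 0.908 and 0.2396 / 0.2424 = 0.988.

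**3. Other selection rules.** Further null simulations, also with 12 covariates, gave:

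- 33 per arm, 4,000 trials, treatment in the model (backward p < 0.05, backward p < 0.20, forward AIC): 6.4–8.0%. With baseline fixed: 5.1–5.2%.
- N = 66 and 80, 2,000 trials per setting, the same three rules: 5.6–8.2% with treatment in the model, 4.0–5.4% with it left out.
- N = 66 and 80, 2,000 trials per setting, backward selection: 5.3–7.3% with treatment in and the standard error 4–11% too small; 4.2–5.5% when selection ignored arm; 4.6–5.4% with baseline fixed.

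Taken together, one automatic selection with treatment in the model gives about 5–8%, with the standard error 2–11% too small.

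**4. Cross-check.** If the standard error is too small by a factor r, a nominal 5% test rejects with probability about 2 × [1 − Φ(1.96 r)]. This gives 5.5% for r = 0.98, 7.4% for r = 0.91 and 8.1% for r = 0.89, in line with the simulated rates.

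**The case against.** The strongest reply is that inflation depends on a rule the protocol does not state. Clustering of covariates need not use the outcome at all, and the text does not say that treatment is in the model during selection. Selection that ignores arm kept type I error near 5% in every run. This stands. A reader might infer that the plan must produce standard errors that are too small; the document supports only that it permits them.

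A reader might also take the highest simulated rates (8.1–9.0% for the best of three routes, 7.5–10.0% for the best of six models) as the expected effect. Those rates assume that the most favourable result is kept. A combination of methods is not a plan to do that, so they show the extreme and not the likely size.

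The abstract describes the primary analysis as a comparison of mean change between groups and mentions no covariates, and the sample size uses an unadjusted comparison. One could read these as the real primary analysis. Neither says that the analysis is unadjusted, however, and the Analysis plan section still gives effectiveness to the mixed model. At most they make the status of the selected model less clear; they do not fix its covariates.

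Two further inferences are not supported. All seven secondary outcomes are on the candidate list, so a reader might suspect that follow-up values would enter as covariates. The recruitment section calls the screening measurements baseline data, and the repeat measurements are collected to assess the secondary outcomes. Nor would dropping baseline step count as a covariate invalidate the comparison: the model addresses change, and the likely loss is precision.

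Finally, covariate detail is often left to a statistical analysis plan. Here, though, the article is not silent: it commits to data-driven selection for the model that tests the intervention.

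**Conclusion.** The point holds in a limited form and should be fixed. It is certain from the text that the effectiveness model is open-ended: 12 candidates, none forced in, no selection rule stated and no blinding of selection to arm. The understated standard error is a possibility that the wording leaves open. For one automatic procedure with treatment in the model it amounts to roughly 0 to 3 percentage points of extra type I error.

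These sizes are indicative. They rest on the assumed covariate correlation and prognostic strength, and on stepwise regression standing in for an unspecified mix of clustering, trees and selection within a mixed model. The missing-data sensitivity analysis does not bear on the problem, because it does not address the choice of covariates.

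**What to change.** State the covariates of the primary model before the data are examined: at least baseline step count, with age and gender if wanted, all taken from screening or the baseline week. Remove the phrase that makes adjustment discretionary. Move clustering, tree-based methods and variable selection to a separate exploratory analysis of predictors of change, and state that it cannot alter the primary estimate. No treatment-by-week term is needed to cure this problem.

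If data-driven selection must stay in the primary model, a fully written algorithm run blind to arm would protect the type I error, but the model would still be unknown until the data are in. Fixing the covariates is simpler.

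The cost is a change of wording, plus at most a small loss of precision if a useful covariate is left out. The exploratory work is still done, and the sample size stays at 33 per arm, or 40 with the dropout allowance.

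### When an intervention participant removes the app or stops sending data, treatment and step record end together, and the missing-at-random model then targets a continued-use effect rather than the promised intention-to-treat effect

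*Protocol article*

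**What the plan says.** Under Sample size and power calculation the protocol article states: "All analyses will be conducted according to the intention-to-treat principle". The same section says that "a sample size of 33 subjects per arm is required to have 80% power at the 0.05 significance level". The target is 1,410 steps, the gap between the two arms' mean changes. The difference combines an expected fall of 470 steps in controls with a rise in the other arm ("increase by 940 (a 20% improvement) amongst those receiving the intervention"). The standard deviation of change is 2,000. The 33 is raised to 40 per arm for losses, with no rate given.

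Under Description of interventions/comparison groups, the same app is installed in both arms: "All participants have the smartphone application downloaded free of charge onto their smartphone but not made visible to the user". After the baseline week only the intervention arm is told how to switch on the display and widget. In both arms steps reach the team when the participant sends them with the app's share function. After baseline this is requested twice, at two weeks and at the end of follow-up. Under Choice and description of the smartphone application, the app is said to run in the background, "allowing researchers to monitor activity without user interaction or effort".

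Under Analysis plan: "It will be assumed that missing data are missing at random and therefore accounted for in the mixed model". Two safeguards follow. One is a look at missing-data patterns with a model for missingness based on the available explanatory variables. The other is a sensitivity analysis by chained equations with predictive mean matching, described as assuming data missing not at random.

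**The concern.** An intention-to-treat effect needs each participant's steps for the whole follow-up, including weeks after the intervention has been given up. Here the visible app is the intervention and the app is also the only step counter described. An intervention participant who switches it off, uninstalls it or no longer sends data ends both at once. Someone who removes it after the two-week share may contribute nothing for the last five of the seven weeks.

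A mixed model under missing at random predicts those weeks from the participant's own earlier steps and from intervention participants who are still recording. This answers what would have happened had recording, and with it use of the app, continued. If steps fall back after stopping, that answer is larger than the intention-to-treat effect. Giving up an app because it is unhelpful or irritating is part of how a behavioural intervention performs in practice, and this particular reason for loss arises mainly where the app is visible.

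**Working it through.** **1. The plan's own figure.** Two-sample comparison of means, two-sided 0.05, 80% power, difference 940 − (−470) = 1,410, SD 2,000. The normal approximation gives 32 per arm. The noncentral t gives 33 (power 0.805; 32 per arm gives 0.793). The stated 33 is reproduced, and the sample size is not in question. The loss implied by going from 33 to 40 is 7/40 = 17.5%.

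**2. Inputs the article does not give.** These are the share *d* of the intervention arm that stops without further data, the share *r* of the effect kept afterwards, and the time of stopping. All three are assumptions below. Controls are taken as fully observed unless stated.

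**3. Stopping at the start.** Intention-to-treat difference = 1,410 × [1 − *d*(1 − *r*)]. The missing-at-random target stays at 1,410.

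| Share stopping | ITT, r = 0 | Excess | ITT, r = 0.5 | Excess |
|---|---|---|---|---|
| 5% | 1,340 | 70 (5%) | 1,375 | 35 (3%) |
| 10% | 1,269 | 141 (11%) | 1,340 | 70 (5%) |
| 17.5% (7 of 40) | 1,163 | 247 (21%) | 1,287 | 123 (10%) |
| 30% | 987 | 423 (43%) | 1,198 | 212 (18%) |

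Check for 7 of 40 with r = 0: the intervention-arm mean change is (33 × 940 + 7 × (−470))/40 = 693, and 693 + 470 = 1,163.

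**4. Stopping after week 2 of 7.** With r = 0 and the effect averaged over follow-up, the excess is 247 × 5/7 = 176. The intention-to-treat difference is 1,410 − 176 = 1,234, and 176/1,234 = 14%.

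**5. Stopping spread evenly over the seven weeks.** This was simulated with 40,000 per arm, weekly SD 2,000, within-person correlation 0.7, r = 0, stopping unrelated to earlier steps, and missing-at-random estimation by sequential regression within the arm. At 17.5% stopping the true difference averaged over follow-up is 1,259 and the model gives 1,399, an excess of 140 (11%). In week 7 alone the figures are 1,155 and 1,403. At 10% and 30% stopping the averaged figures are 1,339 against 1,419 and 1,167 against 1,409. The model's answer stays near 1,410 whatever share stops.

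**6. Losses in both arms.** Let *p* be the share of an arm with missing weeks and *s* the amount by which their true steps lie below the model's prediction. Then net bias ≈ *p*(intervention) × *s*(intervention) − *p*(control) × *s*(control). The figures above set the second term to zero. Equal products would cancel.

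**7. Do the planned safeguards detect this?** The missingness model uses observed variables, so it cannot show dependence on steps that were never recorded. Predictive mean matching fills a gap with an observed value from a participant with a similar prediction. Unless a shift or a reference arm is specified, the result is in effect another missing-at-random analysis, despite its label.

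**The case against.** A reader might infer that anyone who stops using the app leaves no step data. The documents do not support that. The counter runs in the background and works while hidden. A participant who merely ignores the display still records steps, and those off-treatment days enter the model as intention-to-treat requires. Nor does the article say that data from participants who stop are discarded. Both arms are asked to carry the phone and send their data, and all participants are invited to the follow-up visit. These objections stand, and they confine the point to participants who switch off or remove the app or send nothing.

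A reader might also take 21%, or 43% at 30% stopping, as the expected inflation. Both figures need stopping from the start and complete loss of effect, and 30% exceeds the loss the sample size allows for. The model also uses each person's earlier weeks, so a decline before removal is partly carried forward. Controls use the same app and can be lost too, so even the direction of the net bias is not guaranteed. For scale, the standard error with 40 per arm is about 2,000 × √(2/40) = 447 steps, well above most of these shifts. That bears on how visible the bias would be. It does not remove the bias.

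Finally, an article may leave the handling of discontinuation to the full protocol, and a not-at-random analysis is already announced. The first part stands as far as missing detail goes. But the article does fix a primary assumption that does not match its stated principle, and the method it names for testing that assumption does not test it.

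**Conclusion.** The point holds in this limited form. For intervention participants who switch off or remove the app, or stop sending data, the primary model estimates a continued-use effect. That effect can exceed the intention-to-treat effect the article promises, and the named sensitivity analysis does not cover the gap.

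The size cannot be settled from the documents. With 7 of 40 stopping, a plausible range runs from about 10% (stopping at the start, half the effect kept) through 14% (after week 2, none kept) to 21% (at the start, none kept). All of these assume no offsetting loss among controls. If nobody stops recording, or if steps do not fall after stopping, there is no overstatement.

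**What to change.** Under Description of interventions/comparison groups, separate ending the feedback from ending measurement. An intervention participant who no longer wants the feedback is asked to return the app to its hidden baseline-week state, leave it recording and keep sharing data at the planned times. Those steps are included in the primary mixed model.

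Under Analysis plan, make the not-at-random analysis explicit. For intervention participants who stop and send nothing, impute the missing weeks from the control-arm mean change, or apply a stated downward shift. Report the number with missing weeks by arm alongside it, since the net bias depends on both.

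The cost is a sentence in the phone script, a wording change, one more analysis and a possibly smaller estimate. Enrolment had already begun when the article was written, so the measurement change can help only participants still to be followed. The analysis change can cover everyone. Some participants will still remove the app, so the second change is needed even if the first is made.
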